## 2.2 Secondary analyses of LDL-c based endpoints

- Primary endpoint  $\Delta_{LDL}$  at 12 months.
  - Complete case analysis. Use only those subjects without missing data at 12 months
  - Repeat primary analysis
    - without adjustment for baseline LDL-c or site:
    - with adjustment for baseline LDL-c only
    - with adjustment for site only
    - with additional adjustment for race, gender, income and education (basis demographic and socio-economic status)
- Post-intervention of  $\Delta_{LDL}$  at 18 months.: Repeat primary analysis
- Across visits: Mixed effects model of  $\Delta_{LDL}$  as a function of study visit and intervention arm. Include an interaction term between visit and intervention arm. Use intervention period only. Test for differences between each intervention arm and control across the visits.
- Subgroup analyses for intervention period: Mixed effects models separately for subgroups of:
  - Gender
  - Race
  - Income stratified at  $< \$50,000$   $\geq \$50,000$
  - LDL-c at baseline: Use  $< 160$  mg/dl versus  $\geq 160$  mg/dl. These cutoffs chosen in order to target individuals with poorer LDL-c and also to have sufficient sample size to make meaningful comparisons across arms.
  - ASCVD or not
  - Penn Medicine versus Lancaster General

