**Randomization.** Randomization will be performed through the Way to Health platform. Randomization will be stratified by employer (should more than one employer be involved to recruit a sufficient number of participants) and will use block randomization with variable block sizes. After reviewing the intake data and LDL, research staff will notify each participant of assignment using their preferred means of communication. All participants will receive an electronic pill container through the mail and will receive careful instructions about study procedures for their assigned arm. Throughout the study, coordinators will remain available to answer questions about the electronic pill container use and other study procedures.

**LDL Measurement Schedule.** Participants will have six LDL laboratory checks, at months 0, 3, 6, 9, 12 and 18 months. To maximize the likelihood that these LDL measurements are completed, the Way to Health participant tracking system will remind the study coordinators when each participant is due to visit a lab. We will obtain extensive contact information including preferred mode of communication - from each participant and update it at each follow-up visit. Participants who miss scheduled LDL checks will receive four reminders. Patients will receive \$50 after enrollment, initial blood work, and setting up the Glow Caps. A subset of participants will receive \$100 after enrollment to test whether higher participation incentives increase recruitment rate. Participants will receive \$50 for each subsequent lab check and \$75 for the 12 month LDL check (the primary outcome).

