### **Analysis Plan**

Data analysis plans. We will explore and describe participant attributes across the 4 arms using graphical approaches and summary statistics (means, medians, standard deviations and the interquartile range). The primary analysis will be intent-to-treat using a linear regression analysis of the effect of treatment assignment on the outcome of change in LDL from baseline to 12 months. The model will be stratified by center and baseline will also be added as a covariate in order to improve efficiency of the analysis. Secondary analyses will adjust for measures of socioeconomic status (SES) and educational attainment (EA). We will explore whether SES and EA act as effect modifiers. We will assess model fit using standard linear regression diagnostics. In additional exploratory analyses, longitudinal models will examine the series of LDL values over time, to determine the shape of the trajectory and consider whether those trajectories differ by treatment group. All hypothesis tests will be two-sided. As a secondary analysis, we will compare the effect of the interventions vs. control among the subgroup of patients who are African-American and/or Hispanic. To maximize the power for this exploratory analysis, we will pool participants in all three incentive arms and compare to control participants. Missing data: Given low rates of drop-out in our other financial incentive studies and because this trial is low-risk, we anticipate low rates of drop-out. As with our other studies, we are diligent in proactively encouraging complete follow-up. Generous participation incentives, as well as multiple reminders

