## 2 Inference

### 2.1 Primary outcome

- Linear regression model of primary outcome,  $\Delta_{LDL}$ , for month 12 of the study as a function of study arm with baseline LDL-c and population included in the model (Penn Medicine & Lancaster General)
- Primary analysis uses multiple imputation (MI) to adjust for missing data
  - Describe subjects who are missing 12-month LDL-c data (within 60-day window)
  - Imputation model: includes arm assignment, and all of the baseline covariates described above.

- Hypothesis testing as described in the protocol and in previous Habit Formation Trial. Use a family-wise type I error rate of 0.05.
  - Compare each arm to control using Holm-Bonferroni correction
  - Compare any arms that are significant (adjusted  $p < .05$ ) to each other using Tukey's Honest Significant Difference.

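### The across-visit and subgroup mixed models of LDL change do not list baseline LDL as a covariate, a small and avoidable loss of precision in secondary analyses

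*Combined protocol and SAP*

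**What the plan says.** The SAP's primary model (section 2.1) regresses 12-month LDL change "as a function of study arm with baseline LDL-c and population included in the model (Penn Medicine & Lancaster General". The protocol's Analysis Plan gives the reason for the baseline term in its primary regression: "baseline will also be added as a covariate in order to improve efficiency of the analysis".

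SAP 2.2 then sets out the secondary analyses of LDL.

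- **Across visits.** A mixed-effects model of LDL change over the intervention period is specified "as a function of study visit and intervention arm. Include an interaction term between visit and intervention arm". Its stated purpose is "Test for differences between each intervention arm and control across the visits". Neither baseline LDL nor site is in the list of terms.
- **Subgroups.** The bullet reads "Subgroup analyses for intervention period: Mixed effects models separately for subgroups of", followed by six factors: gender, race, income, baseline LDL-c below or from 160 mg/dl, ASCVD status, and site. No model terms are given.
- **18 months.** The instruction is "Repeat primary analysis", which carries both covariates over.
- **Adjustment variants.** Versions without baseline or site, and with only one of them, are planned for the 12-month endpoint only.

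The protocol introduces the longitudinal work with "In additional exploratory analyses, longitudinal models will examine the series of LDL values over time" and names no covariates for it. In the protocol's Procedures section, the text on confounders lists baseline LDL among variables to be compared across arms, with adjustment where needed. That is a conditional promise and not a model specification.

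**The concern.** When the outcome is change from baseline, baseline is the obvious prognostic covariate: someone who starts high tends to fall further, whatever the arm. The SAP uses it in the primary and 18-month analyses. The across-visit model has its own list of terms, and baseline is not on it. An analyst who follows the text fits the model without baseline; one who adds it makes an unplanned choice.

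What is at stake is precision and consistency. The arm-versus-control tests over months 3 to 12 would have wider intervals than necessary. So would the subgroup estimates, if those models share the across-visit specification. Subgroups are small, and chance differences between arms in baseline LDL are larger there. A secondary result could also differ from the primary one partly because the covariates differ.

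**Working it through.** **The plan's own figure.** The documents give no precision or power figure for the mixed models. The nearest is the protocol's power statement for the 12-month comparison: 160 per arm, SD 28 mg/dl, difference 10 mg/dl, two-sided α = 0.05/3.

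- SE = 28 × √(2/160) = 3.13 mg/dl.
- Power = Φ(10/3.13 − 2.39) ≈ 78.8%, against a stated figure of at least 80%. Read per comparison, it reproduces to within about one point.
- The protocol does not say whether 28 is the SD of LDL level, of change, or of a baseline-adjusted residual.

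**Inputs for the precision check**

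- Visits: "Participants will have six LDL laboratory checks, at months 0, 3, 6, 9, 12 and 18 months" (protocol, Design). Four of these are follow-up visits in the intervention period.
- Entry LDL of at least 100 mg/dl (protocol, Key inclusion criteria). The route requiring an LDL of 190 is ignored here.
- Assumed, because the documents do not give them: correlation ρ = 0.3, 0.5 or 0.7 between any two visits; equal variance at every visit in the source population; source mean 115 and SD 35 mg/dl; a linear relation; no missing visits.

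**Effect of the entry limit on baseline variance.** With a = (100 − 115)/35 = −0.429, λ = φ(a)/[1 − Φ(a)] = 0.364/0.666 = 0.547. The baseline variance among entrants, as a fraction of the source variance, is v = 1 − λ(λ − a) = 1 − 0.547 × 0.975 = 0.467.

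**Formulas, in units of the source variance.** Change equals −(1 − ρ) × baseline plus a residual.

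- With baseline in the model: A = 1 − ρ² at one visit. For the mean of four visits, A = m − ρ², where m = (1 + 3ρ)/4.
- Without baseline: U = A + (1 − ρ)² v.
- SE ratio, adjusted to unadjusted: √(A/U).

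| ρ | One visit: A / U | SE ratio | SE reduction | Mean of months 3–12: A / U | SE ratio | SE reduction |
|---|---|---|---|---|---|---|
| 0.3 | 0.910 / 1.139 | 0.894 | 11% | 0.385 / 0.614 | 0.792 | 21% |
| 0.5 | 0.750 / 0.867 | 0.930 | 7% | 0.375 / 0.492 | 0.873 | 13% |
| 0.7 | 0.510 / 0.552 | 0.961 | 4% | 0.285 / 0.327 | 0.933 | 7% |

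In participants, the single-visit gain is U/A − 1, or about 25%, 16% and 8%. If 28 is the SD of unadjusted change, the single-visit SE of 3.13 mg/dl becomes about 2.80, 2.91 or 3.01.

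A simulation of 600 trials with 160 per arm under the same assumptions gave SE ratios of 0.91, 0.95 and 0.96 at month 12, and 0.81, 0.88 and 0.93 for the four-visit mean. These are close to the table, with slightly smaller gains at the lower correlations.

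**Without the entry limit** (v = 1), the single-visit variance ratio is (1 + ρ)/2 and the SE reductions would be 19%, 13% and 8%. For the four-visit mean they would be 34%, 23% and 13%. These overstate the gain in this population.

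**Site.** Suppose the two sites are equal in size and differ by d in mean change. Then R² = 0.25 d²/28² and the SE ratio is √(1 − R²). For d = 5 mg/dl this is √(1 − 0.008) = 0.996; for d = 10 it is √(1 − 0.032) = 0.984.

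**The case against.** The strongest reply is that little depends on this. The models are secondary in the SAP and exploratory in the protocol. The primary and 18-month analyses keep both covariates. The change score already subtracts baseline, so the adjustment is inefficient rather than absent. The protocol provides for adjustment if baseline variables turn out to be unbalanced. The 12-month variants in SAP 2.2 will show how far the covariates move the estimate at that visit. The SAP is also silent on baseline here rather than excluding it, and that the subgroup models share the across-visit terms is an inference. All of this stands, and it is why the point is minor. It does not supply the missing covariate: adjusting only when imbalance is seen is not a specification, and the variants cover month 12 alone.

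Some stronger readings are tempting but not supported:

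- **That the contrasts are biased.** Randomisation keeps the unadjusted arm contrasts unbiased.
- **That the entry limit makes baseline matter more.** It does the reverse. Selecting on baseline shrinks its variance and weakens its correlation with change, from −0.50 to about −0.37 at ρ = 0.5 under the assumptions above. Regression to the mean occurs in every arm and does not affect the contrasts.
- **That omitting site costs real precision.** Nothing in the documents shows this, and the assumed differences above give under 2%.
- **That the SAP contradicts the protocol.** The efficiency reason is attached to the primary regression, and the protocol promises no covariates for the longitudinal models.

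**Conclusion.** The omission is in the text, and no other section restores baseline LDL to these models. The cost is precision only. Under the stated assumptions, adding baseline LDL would lower the standard error by about 4% to 11% at one visit and 7% to 21% for the mean of months 3 to 12. The four-visit mean is the closer match to a test across the visits, though the SAP does not say whether that test is of an average effect or a joint test over visits.

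The size rests on an undocumented correlation, an assumed source distribution and complete data; the direction does not depend on the particular values taken. In the subgroups the gain is less certain, because their model terms are not stated and the split at 160 mg/dl already conditions partly on baseline. Severity is minor: this is a free improvement to secondary analyses, and the primary conclusion does not depend on it.

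**What to change.** In SAP 2.2, state that the across-visit mixed model includes baseline LDL-c and a baseline-by-visit term alongside arm, visit and arm-by-visit. State that the subgroup mixed models use the same terms. Add site to both for consistency with SAP 2.1, except in the separate Penn Medicine and Lancaster General models, where site is constant and cannot be fitted.

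The cost is a sentence or two of SAP wording. Both variables are already in the primary model, so no new data and no change to conduct are needed.

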
suggests that a reduction in 10 mg/dl in LDL potentially reduces CVD events by 5%. We present results from a two-step approach to the power calculation intended to detect differences of 10 mg/dl or greater between the control and each intervention arm, as well as a 5 to 10 mg/dl difference between the most and least effective intervention arms. Thus Step 1 compares each of the intervention arms versus control (3 comparisons); Step 2 compares each of the intervention arms to each other arm (3 additional comparisons). For these sample size estimates, we assumed a standard deviation of 28 mg/dl (based on a prior RCT). The nominal experiment-wise two-sided Type 1 error rate of 0.05 was maintained in step 1, by using a Bonferroni correction (i.e.,  $\alpha=0.017$ , derived as  $0.05/3$  for 3 comparisons) and in Step 2 by using Tukeys honest significant difference. Many possibilities exist for differences between the three interventions and control; the table below considers three possibilities for a sample size of 160 per group. For differences of 10 mg/dl or larger between intervention and control, simulation studies indicate at least 80% power to detect differences between all 3 interventions and control. For differences of at least 10 mg/dl between interventions, we have at least 90% power to detect at least one difference among arms; for differences of 5 mg/dl or larger we have 82% power to detect at least one difference among arms. To ensure our sample size of 160 for the 12 month endpoint, we assumed a dropout rate of 14.5 % and inflated the sample size to 187 in each arm ( $n=748$  in the entire study) . Sensitivity Analyses: Between November 2015 and July 2016 the device failed at rates that exceeded rates obtained in our earlier studies. We anticipated that this might increase the variance of the primary outcome, with some subjects perhaps responding positively with increased compliance to statin medication and some negatively with decreased compliance. Positive responses might reflect increased intervention from study staff, or the swapping out of one device for another spurring increased compliance. Negative responses might reflect frustration, particularly on the Process arm or the Process & Outcome arm, with the inconsistent devices. We note that our completion rates for lab visits are close to our expected rates of 85%, suggesting that the device issue has not had an impact on subject retention. APPROACH 1: As a sensitivity analysis, we increased our assumed variance by 7% (SD 29 versus SD of 28) and we decreased our effect size in the Process alone and the Process & Outcome arms by 10%. Given that only XX subjects were affected for over a month, we believe this to be a very conservative calculation of the negative impact of the device issue. Table 2 above shows that, while our power has declined somewhat, we still have close to 80% power or APPROACH 2: As a sensitivity analysis, we increased our assumed variance by 15% (SD 30 versus SD of 28). Given that only XX subjects were affected for over a month, we believe this to be a reasonable assumption. Our study was designed to detect differences of 10 mg/dl between control and treated group as this difference is deemed clinically relevant. Table 3 below shows there is some decline in power, but overall we retain good power to complete the study successfully under a number of scenarios.

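### The SAP models each subgroup separately and specifies no arm-by-subgroup interaction, so it does not test whether the incentive effect differs between groups

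*Combined protocol and SAP*

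**What the plan says.** SAP section 2.2, under secondary analyses of LDL-c, reads "Subgroup analyses for intervention period: Mixed effects models separately for subgroups of" and then lists gender, race, income (cut at $50,000), baseline LDL-c (cut at 160 mg/dl), ASCVD status and site. The preceding item, the model across visits, has a visit-by-arm interaction. No arm-by-subgroup term appears anywhere in the SAP. The LDL-c cut is justified partly by the need for enough participants to compare arms, so comparisons of arms within strata are intended.

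The family-wise error rate of 0.05 in SAP section 2.1 belongs to the primary outcome. No significance level, multiplicity rule or reading rule is given for subgroups.

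The protocol's Analysis Plan says of socioeconomic status and educational attainment: "We will explore whether SES and EA act as effect modifiers". Its Procedures section adds that baseline variables may be effect modifiers, meaning that they predict how large the effect is in different participants. Neither place names a model or test. In the SAP's subgroup list, income is the only socioeconomic measure and education is absent. By contrast, SAP section 3 does plan to estimate a change in effect size for exposure to faulty devices.

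**The concern.** Effect modification is a difference between two effects. Fitting a model in each stratum gives the two effects but not, as planned, their difference, its confidence interval or a test. What the reader sees is a set of stratum results side by side, and the natural comparison is which are significant. That comparison is unreliable, because each stratum holds only part of the sample and an effect common to everyone will often reach significance in one stratum and miss it in the other. At stake is what the trial reports about who responds to which incentive, for example by income, race or baseline LDL-c.

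**Working it through.** **Inputs from the protocol (power paragraph under Accrual).** The trial is "intended to detect differences of 10 mg/dl or greater between the control and each intervention arm". The SD is 28 mg/dl, and "the table below considers three possibilities for a sample size of 160 per group". For dropout, "we assumed a dropout rate of 14.5 % and inflated the sample size to 187 in each arm". Step 1 uses 0.05/3 = 0.017 per comparison, two-sided.

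**The plan's own figures.**
- n per arm = 2 × (28/10)² × (2.387 + 0.842)² ≈ 164, against 160 stated.
- Power per comparison at 160: SE = 28 × √(2/160) = 3.13; 10/3.13 = 3.19; Φ(3.19 − 2.39) ≈ 0.79, against 80% stated.
- 160/(1 − 0.145) = 187.1 per arm; 4 × 187 = 748.

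The inputs reproduce as per-comparison power, so they are a fair basis for the subgroup check.

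**Assumptions not in the documents.** Stratum splits from 50:50 to 20:80; 0.05 two-sided per within-stratum test; an effective SD from 28 down to 20 mg/dl, to allow for baseline adjustment and repeated measures; 160 per arm, or up to 187 per arm if partial data contribute.

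**Formulas.** With n₁ and n₂ per arm in the two strata and the same true effect of 10 mg/dl in both:
- power in stratum i: pᵢ = Φ(10/(SD√(2/nᵢ)) − 1.96)
- chance of significance in exactly one stratum: D = p₁(1 − p₂) + p₂(1 − p₁)
- SE of the interaction = SD × √(2/n₁ + 2/n₂)

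**Discordance D when there is no true subgroup difference.**

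| SD | n per arm | Split | p₁ | p₂ | D |
|---|---|---|---|---|---|
| 28 | 160 | 50:50 | 0.617 | 0.617 | 0.472 |
| 28 | 160 | 30:70 | 0.417 | 0.762 | 0.544 |
| 28 | 160 | 20:80 | 0.298 | 0.815 | 0.628 |
| 24 | 160 | 50:50 | 0.750 | 0.750 | 0.375 |
| 20 | 160 | 50:50 | 0.885 | 0.885 | 0.203 |
| 20 | 160 | 20:80 | 0.516 | 0.979 | 0.485 |
| 28 | 187 (93 per half) | 50:50 | 0.683 | 0.683 | 0.433 |
| 24 | 187 (93 per half) | 50:50 | 0.811 | 0.811 | 0.307 |
| 20 | 187 (93 per half) | 50:50 | 0.926 | 0.926 | 0.137 |

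With no effect anywhere, D = 2 × 0.05 × 0.95 = 9.5%. A stricter 0.0167 per test does not help: D is 0.494 at SD 28 and 50:50, and reaches 0.674 at SD 24 and 20:80.

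**Interaction test, same inputs.** Its false-positive rate is 5% per contrast by construction. At SD 28, 160 per arm:
- 50:50: SE = 28 × √(2/80 + 2/80) = 6.26. Power for a 10 mg/dl difference in effects = Φ(10/6.26 − 1.96) ≈ 36%. Difference detectable with 80% power = 6.26 × (1.96 + 0.84) = 17.5 mg/dl.
- 20:80: SE = 7.83, power 25%, detectable difference 21.9 mg/dl.

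**Across the six factors.** In 3,000 simulated trials (six independent 50:50 factors, three arms against control, one visit, SD 28, effect 10 everywhere), 48% of the 18 contrasts were discordant and 98% of trials had at least one discordant pair. Testing 18 interaction contrasts unadjusted gave at least one false positive in 55% of trials. One joint test per factor lowers this to 1 − 0.95⁶ = 26% if the tests are independent.

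**The case against.** Several points on the other side stand.

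- **No reading rule.** A reader might infer that the plan commits the sponsor to declaring an incentive effective in one group and not in another, or to reading each subgroup by its own p-value. The documents do not support this. The SAP sets no subgroup threshold, success criterion or rule for comparing strata. The within-stratum estimates are valid, and a difference could be derived from them afterwards. The error arises only if significance is contrasted across strata.
- **Effect modification is not ignored.** The protocol states the intent for socioeconomic status and education, which partly covers income. It names no method, and that sentence does not reach gender, baseline LDL-c, ASCVD or site.
- **The 47% is not a calculation of the planned model.** It is a single-visit comparison, whereas the SAP plans repeated-measures models over the intervention period. These may be more precise, and unequal splits push the other way. The documents give neither the splits nor the within-subject correlation, so only a range can be defended.
- **Multiplicity is a separate matter.** With no effect at all, about 64% of simulated trials had at least one nominally significant result among 36 within-stratum contrasts. That does not measure the cost of omitting the interaction, and 36 assumes two levels per factor although the SAP gives no race categories.
- **Status.** The analyses are secondary, and the protocol calls its own race/ethnicity comparison exploratory.

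What remains is that the SAP chose a method that does not test the question the protocol raises, and a better one is available on the same data.

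**Conclusion.** The point holds as a gap in the analysis method. It does not establish that false claims will follow. With an identical true effect of 10 mg/dl in both strata and 0.05 per test, contrasting significance between separate models would mislead in roughly 14% to 63% of contrasts, against 5% for an interaction test. The low end needs an SD of 20 mg/dl, even splits and data from all 187 per arm. The high end takes SD 28, 160 per arm and a 20:80 split. Even the low end is more than twice the interaction test's error rate. The primary analysis has its own error control and is untouched. Because interaction power is low, the trial will seldom settle who benefits more, and interaction estimates with confidence intervals would make that visible.

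**What to change.** Replace the separate models in SAP section 2.2 with the following.

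1. For each factor, fit one mixed model on all participants with arm, visit, factor, arm-by-factor and visit interactions, baseline LDL-c and site.
2. Report the arm-by-factor interaction estimates with 95% CIs and one joint interaction p-value per factor (3 degrees of freedom for a two-level factor with three arms against control).
3. Show the subgroup estimates from that same model, without significance claims within subgroups.
4. Label the analyses exploratory, and state that six unadjusted joint tests carry about a 26% chance of at least one false positive.

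The cost is a few lines of SAP text and slightly different code, with no new data. The drawback is low power, about 36% for a 10 mg/dl difference in effects at 50:50, so most interaction tests will be non-significant. The text should say that this is not evidence of equal effects.

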LDL decreases at least 10 mg/dl in the 3 months since the last visit. Over a year, these payments will be equivalent in magnitude to those in the process arm. The 3-month payment for the Outcome arm (arm #2) will be \$126, while the payment for the Process with Outcomes Incentive arm (arm #3) will be half this value, or \$63. Notably, if a participant in the Outcomes arm or the Process plus Outcomes arm achieves a reduction in LDL 20 mg/dl during one quarter of the trial and that reduction persists during the next quarter, the participant would be eligible for the outcome incentive at the end of both quarters, even if no further reduction in LDL took place during the second quarter. For instance, if a patient in the Outcome arm had an LDL decrease from 150 to 130 mg/dl between baseline and month 3, and also had an LDL of 130 mg/dl at month 6, that person would receive the incentive payment at month 3 and month 6. Participants in the intervention arms will be informed if they fail to meet adherence or LDL goals, and thereby are not eligible for payments. Providing this feedback may also improve adherence by taking advantage of anticipated regret.

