
receive the statin medication but not take the pills, which could lead to overestimation of adherence; and 2) the problem that when prescribing doctors lower the statin dose, patients may continue to use existing pills (e.g. cutting a 40mg tablet into 20 mg half-tablets and taking the half-tablets) and refill the medication at a longer interval, leading to underestimation of adherence. However, the MPR offers complementary information about adherence and will be analyzed both during the 12 months of the intervention and for an additional 6 months post-intervention. Adherence to non-statin medications assessed through the Medication Possession Ratio (secondary outcome). It is unknown whether financial incentives for statins and LDL cholesterol may lead to positive or negative spill-over effects for other medications. For instance, a focus on taking statins could lead participants to neglect the need to take their other medications. On the other hand, by helping participants reinforce good adherence habits for statins, participants might be more likely to take other medications as well. Comparisons of the MPR for non-statin medications across treatment arms will inferences about the spill-over effects of process vs. outcomes-based financial incentives. We will specifically examine spill-over effects related to other medications commonly used to lower CVD risk, e.g. blood pressure medications. Potential confounders and mediators. Randomization should balance measured and unmeasured confounders across study arms. However, we will measure potential confounders during study enrollment and compare their distributions across arms and perform adjustments if necessary. We will have data on participant demographics, self-reported socioeconomic status, co-morbidities, baseline MPR for statins and other medications, and baseline LDL cholesterol. Notably, these variables may also serve as either effect-modifiers (predicting the magnitude of an interventions effect across participant groups) or mediators (variables related to mechanisms whereby the intervention works) in the intervention-outcome pathway. For variables believed to be mediators, we would not make adjustments (see Data Analysis Plan, § IV.E.2.). Participant characteristics. Baseline data will be collected through the Way to Health internet portal and/or through phone interviews with study coordinators. Baseline data will be comprised of self-reported demographics (e.g., age, sex, race/ethnicity, income, education, marital status, employment, health insurance) and co-morbidities and medication adherence questions. Participant Characteristics. At the 6, 12 and 18 month interviews, participants will complete a medication adherence questionnaire. During the 12-month interviews, we will also collect data from participants about time spent using the study device, getting labs drawn, and interacting with the Way to Health interface; these time estimates will be used for cost-effectiveness analyses.

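### SAP 2.2 examines variation in the incentive effect with starting LDL only through separate models either side of 160 mg/dl, so it never tests that variation and uses baseline LDL inefficiently.

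*Combined protocol and SAP*

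**What the plan says.** SAP 2.2 introduces the subgroup work with "Subgroup analyses for intervention period: Mixed effects models separately for subgroups of" and lists six factors. Baseline LDL is one of them, cut at 160 mg/dl, with the reason "These cutoffs chosen in order to target individuals with poorer LDL-c and also to have sufficient sample size to make meaningful comparisons across arms". The only interaction in that section belongs to the across-visits model: "Include an interaction term between visit and intervention arm". It concerns visit, not baseline LDL.

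In SAP 2.1 baseline LDL enters the primary model as a main effect only: the 12-month change is modelled "as a function of study arm with baseline LDL-c and population included in the model".

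The protocol's Procedures section counts baseline LDL among the baseline variables of which it says "Notably, these variables may also serve as either effect-modifiers", but gives no model for it. The protocol's Analysis Plan names two modifiers to examine, and baseline LDL is not among them: "We will explore whether SES and EA act as effect modifiers". SAP 2.3 describes adherence, not the effect on LDL, by baseline LDL.

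The outcome payment in arms 2 and 3 is earned when "LDL decreases at least 10 mg/dl in the 3 months since the last visit", with a carry-over rule for a fall of 20 mg/dl that persists into the next quarter.

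**The concern.** Two separate subgroup models give two effect estimates per arm and no test of whether they differ. A significant result in one stratum and a non-significant one in the other can easily be read as a difference when the data show none. A real gradient can equally pass unremarked.

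The cut adds a second problem. Within each stratum all starting values are treated alike, so 101 and 159 are pooled while 159 and 161 are separated. Adding an arm-by-stratum test would supply the missing comparison but would not recover this lost information.

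The modifier is worth examining. A fall of 10 mg/dl is 10/100 = 10% of an LDL of 100, 10/160 = 6.3% of 160 and 10/190 = 5.3% of 190. In arms 2 and 3 the same payment may therefore be easier to earn from a higher start. What is at stake is a statement about who benefits, which could influence how incentives are targeted. The main result is not at stake.

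**Working it through.** **Inputs from the documents.** 160 analysed per arm, SD 28 mg/dl, design difference 10 mg/dl, Bonferroni alpha 0.05/3 (protocol, Power and Sample Size); lower LDL limit 100 mg/dl (inclusion criteria); cut at 160 (SAP 2.2).

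**Inputs assumed.** Baseline LDL is normal, truncated at 100, with parent mean 125-150 and SD 30-35. The residual SD is 26. The effect is linear in baseline LDL, with a slope in mg/dl of effect per mg/dl of baseline.

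**The plan's own figure.** Standard error of a difference: 28 x sqrt(2/160) = 3.13. Then 10/3.13 = 3.19 and power is Phi(3.19 - 2.39) = 0.79, close to the stated 80% when read per comparison. Dropout: 160/(1 - 0.145) = 187.1, against 187 per arm stated. The documents give no power figure for the baseline-LDL subgroups.

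**Information kept by the split.** For a linear gradient this is the squared correlation between baseline LDL and the indicator of 160 or more.
- Parent mean 125, SD 30: after truncation SD 22.9, share at or above 160 15%, information kept 0.53.
- Parent mean 150, SD 35: after truncation SD 30.4, share 42%, information kept 0.67.

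Shape matters. For an untruncated normal the value is phi(z)^2/[q(1 - q)], with q the share at or above 160. This gives 64% at q = 50%, 58% at 30%, 49% at 20% and 43% at 15%. Other shapes bounded below at 100, with shares of about 20-54%, keep about 58-67%.

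**Interaction power, one arm against control, two-sided 0.05.** For a continuous term, z = slope x SD of baseline / [26 x sqrt(2/160)], and the denominator is 2.91. For the split, multiply z by the square root of the information kept. Power is Phi(z - 1.96) + Phi(-z - 1.96).

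Example at the low end, slope 0.3: z = 0.3 x 22.9/2.91 = 2.36, power 65%. Split: 2.36 x sqrt(0.53) = 1.72, power 40%.

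| Slope | Difference in effect, LDL 100 to 160 | Continuous | Split |
|---|---|---|---|
| 0.3 | 0.3 x 60 = 18 mg/dl | 65-88% | 40-72% |
| 0.2 | 12 mg/dl | 35-55% | 21-40% |
| 0.1 | 6 mg/dl | 12-18% | 9-14% |

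The split column assumes that an arm-by-stratum test is added; the SAP has none.

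**Power inside the upper stratum.** Difference 10 mg/dl, unadjusted 0.05, noncentral t. For the mean of four visits the SD is 28 x sqrt((1 + 3 rho)/4), which is 22.1 at rho = 0.5 and 24.6 at rho = 0.7.

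| Share at or above 160 | Per arm | One visit | Mean of four visits |
|---|---|---|---|
| 20% | 32 | 29% | 36-43% |
| 30% | 48 | 41% | 50-59% |
| 40% | 64 | 52% | 62-72% |
| 50% | 80 | 61% | 72-81% |

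**The case against.** The strongest reply is that the SAP does not set out to test effect modification. It sets out to estimate the effect in a pre-specified group with poorer LDL, and separate models do that. This stands as a description of the aim, but results shown for both strata invite a comparison that the plan gives no means of making. The same gap affects the other five subgroup factors.

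Four stronger readings are tempting, and the documents do not support them.
- *The cut throws away a fixed share of the data.* The loss depends on an LDL distribution that the documents do not report and on a linear gradient. If the effect changes abruptly at 160, the split loses nothing.
- *A continuous term would estimate the gradient well.* It would not for moderate gradients. A slope of 0.3 implies an 18 mg/dl range of effect between LDL 100 and 160, large beside a design difference of 10, and at 0.2 power is at best 55%.
- *The sample-size reason for the cut is false.* The sentence explains a trade-off in choosing the cut and states no power, so it cannot be refuted by an 80% standard. It can only be called unsupported by a figure.
- *The fixed payment target proves a gradient.* It applies only to arms 2 and 3. It is judged against the previous visit, so baseline is the reference only at month 3. It makes a gradient plausible, and no more.

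**Conclusion.** The point holds in a limited form. SAP 2.2 has no arm-by-baseline-LDL interaction, so it does not test whether the incentive effect varies with starting LDL. The 160 mg/dl split is also a less efficient basis for such a test than a continuous term if the gradient is roughly linear. With 15-42% of participants at or above 160, under truncated normals, the split keeps about 53-67% of the information. The gain in power from a continuous term is useful at a slope of 0.3 and smaller below it, and neither approach is well powered for moderate gradients. These sizes rest on the assumed distribution, the linear form and a residual SD of 26.

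A reader might infer that the trial's main conclusion is weakened. It is not, because baseline LDL is already a covariate in the primary model and the Holm-tested contrasts do not depend on the subgroup work. This is an inexpensive improvement to a secondary analysis, of low to moderate priority.

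**What to change.** Leave the primary model as it is. An uncentred interaction placed there would turn each arm coefficient into the effect at an LDL of zero and change what the Holm procedure tests.

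Add a separate secondary model, for the 12-month change and for the across-visits mixed model, as follows:
- Include arm by centred continuous baseline LDL. Four arms need three interaction terms, tested jointly.
- Check linearity with a spline.
- Report each arm's effect against control with a 95% CI at pre-set baseline values, for example 120, 160 and 190 mg/dl.
- If imputed data are used, include the arm-by-baseline-LDL terms in the imputation model. SAP 2.1 names none, and leaving them out could pull the interaction towards zero.

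Keep the results below and at or above 160 as a descriptive display labelled exploratory, and either drop the sample-size remark or support it with a number.

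The cost is a few model terms and a paragraph of SAP text, with no new data. The downside is a linearity assumption, which the spline checks.
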